### Concealment mechanism {16b}

Only the statistician and the PI will be aware of the allocation order sequence, while the country co-investigators will be blinded to it, and only the next health facility randomized for rollout will be revealed at each crossover intervention implementation time points, approximately 4 weeks prior, to allow for training on de-escalation of violence techniques.

### Implementation {16c}

The statistician will generate the allocation sequence. HCWs from the participating sites who give consent for participation and who fulfil the inclusion criteria will be enrolled in the study.

## Assignment of interventions: Blinding

### Who will be blinded {17a}

It will not possible to blind the trial participants to the intervention, as participants will be aware of the intervention, the violence de-escalation training they are receiving. The data analyst and the outcome assessors will be blinded to the status of the intervention at the time the outcome is determined.

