### Intervention description {11a}

The intervention consists of two key components, (1) an individual capacity building component delivered through a de-escalation of violence training for HCWs and (2) a code of conduct delivered via a warning board to be implemented at the health facilities and co-developed during the formative phase. HCWs will also receive a refreshment training. The de-escalation of violence training program developed by the ICRC will be used for the implementation [39]. The training will be delivered to HCWs in participating clusters over a half-day workshop. Expert physicians from the MoH and from the research teams from the collaborating universities will co-facilitate the group sessions. The de-escalation of violence training is designed to provide HCWs with the ability to identify tense situations from the outset and to develop skills to defuse them before they further escalate. Furthermore, the training helps to improve the communication skills of HCWs with patients and their families. The training will consist of five modules: (1) an introductory module, (2) understanding violence in health-care settings: causes and effects, (3) learning key behaviors for preventing and de-escalating tense situations, (4) communicating and engaging with people, and (5) taking learning back into the workplace [39]. The training is based on behavioral theory, which states that people learn new behaviors more effectively when their needs are analyzed in a way to ensure their usefulness and applicability. The learnt behaviors provide a direct benefit to the participants when the techniques are practiced during the training. The training material will be contextualized and adapted to include real case-scenarios highlighted during the formative research phase. Once a group of clusters crosses over into the intervention phase, trainers will start the delivery of the training according to a pre-defined delivery schedule (Fig. 1). All HCWs who meet the inclusion criteria will start the training. Along with the de-escalation of violence training, a code of conduct developed during the formative phase will be introduced and displayed in the participating clusters, according to the rollout process.

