### Outcomes {12}

#### Endpoints of study phase 2 (stepped-wedge cluster randomized controlled study)

Primary endpointsNumber of physical and non-physical incidents (verbal abuse, threats, ironic language, provocative or aggressive body language, etc.) reported during the fulfilment of a professional activity in the last 6 months;Secondary endpoints

Type of violenceNumber of physical and non-physical incidents reported by type, by perpetrator, by place, by time, by gender, and during the fulfilment of which activity in the last 6 months;

Coping with violenceLevel of communication skills related to workplace violence among HCWs [40];Clinician Confidence in Coping With Patient Aggression (CCPAI scale) [34]

Psychological endpointsLevel of post-traumatic stress disorders (PTSD) among HCWs (PTSD Checklist for DSM-5) [41–43];Level of burnout among HCWs (Maslach burnout inventory scale) [44, 45];Psychological empathy among HCWs (Jefferson scale of physician empathy scale) [40, 46, 47];Job satisfaction

Organizational endpointsNumber of sick leave spells taken during the study period;Intent to leave among HCWs because of violence (TIS-6 Intention to leave scale) [48, 49]

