## Data collection and management

### Plans for assessment and collection of outcomes {18a}

In all arms, incidence and severity of episodes of violence will be collected by each consenting HCW (self-reported) via the *Aggression log*, longitudinally, during the initial observation period (P1) of 12 weeks and during the whole duration of the trial. This instrument will capture the frequency and description of the incident experienced during the working hours and will allow the staff to judge the severity of the incident via a 100-mm visual analogue scale (VAS). The *Aggression log*, adapted from Morken et al., was customized based on qualitative insights, and simplified for user-friendliness, incorporating feedback from healthcare personnel and experts in both countries, ensuring efficient reporting despite demanding work pressure [50]. The tool will be completed by the HCWs and each time the HCWs are exposed to aggressive behaviors, defined as any verbal, non-verbal, or physical behavior that was threatening or physical behavior that was adding arm. Entries will include time of incident, perpetrator’s gender, type of assault, whether verbal (e.g. verbal threat, insult) or physical, means used by the aggressor and consequences for the victim. Participants will be assured confidentiality and anonymity of their responses through unique identifiers, and a secure reporting system will be established.

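### Item 17a says outcome assessors are blinded, but the primary incident count and its severity rating are self-reported by unblinded health care workers

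*Protocol article*

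**What the plan says.** Item 17a of the protocol article makes two statements in succession. The first is "It will not possible to blind the trial participants to the intervention". The second is "The data analyst and the outcome assessors will be blinded to the status of the intervention at the time the outcome is determined".

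The primary endpoint under Outcomes (item 12) is the number of physical and non-physical incidents "reported during the fulfilment of a professional activity in the last 6 months". The non-physical examples listed there include ironic language and provocative or aggressive body language.

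Item 18a names the instrument and who completes it: "incidence and severity of episodes of violence will be collected by each consenting HCW (self-reported) via the" Aggression log. The same worker grades each incident on a 100-mm visual analogue scale. The periodic questionnaire described in that section also asks workers about their own exposure to violence. No independent assessor of incidents is described.

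The training (item 11a) is "designed to provide HCWs with the ability to identify tense situations from the outset".

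On the allocation, item 16b says "Only the statistician and the PI will be aware of the allocation order sequence", and items 16a and 16c have the statistician generate the sequence. Item 5d gives the statistical analysis to the data management team at the coordinating institute. Item 27 gives data analysts access to the documents that link individuals with encoded data.

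**The concern.** Blinding of outcome assessors guards against a measurement that changes with knowledge of treatment. Here the person who decides whether an event happened, records it and grades it is the trained worker. A reader who takes 17a at face value would credit the primary result with a safeguard it does not have.

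This matters more than usual because the intervention may act on the measuring instrument. Training in recognising tension could make staff log more of the borderline behaviour that the endpoint counts. It could also make them regard such behaviour as managed and log less, or log less because they know what the trial hopes to show. The documents do not say which would dominate.

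Item 6b describes the comparison as before versus after the intervention within each cluster. A shift in logging that starts at crossover coincides with the intervention contrast, so randomising the order of crossover does not remove it.

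**Working it through.** **1. Who assesses what**

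| Outcome | Who determines it | Can 17a's assessor blinding hold? |
|---|---|---|
| Incident count (primary) | HCW, in the log (18a) | No: 17a says participants are not blinded |
| Severity on the visual analogue scale | HCW, in the log (18a) | No, same reason |
| Scales in the periodic questionnaire | Answered by the HCW; item 27 mentions research assistants assigned to data collection | Possible for the interviewer, though the code of conduct is displayed on site (11a) |
| Analysis | Data management team (5d) | Not determinable: 16a–16c, 27 and 5d do not say whether the analyst is also the randomising statistician |

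The first two rows settle the main point without arithmetic.

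**2. Reproducing the pooled power in Table 2**

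Inputs: country-level power from Table 2, a 5% level (two-sided is my assumption; the protocol does not state sidedness), and inverse-variance pooling of the two countries (also assumed). For each country the non-centrality is 1.960 + z(power). The pooled value is the square root of the sum of squares, and pooled power = Φ(pooled value − 1.960).

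- I, 10% quitting: Iraq 0.98 gives 1.960 + 2.054 = 4.014; DRC 0.94 gives 1.960 + 1.555 = 3.515. Pooled √(4.014² + 3.515²) = 5.335; power 0.9996 (Table 2: 0.99).
- B, 30% quitting: Iraq 0.95 gives 3.605; DRC 0.89 gives 3.186. Pooled 4.811; power 0.9978 (Table 2: 0.99).
- R, 10/20/30% quitting: 0.924, 0.898, 0.890 (Table 2: 0.92, 0.90, 0.89).

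The pooling step therefore reproduces to within about one percentage point. The country-level simulations cannot be rebuilt, because the design figure and the simulation supplement are not shown.

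**3. Implied standard error of the pooled log rate ratio**

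The planned ratio is 0.6 (item 14), and |ln 0.6| = 0.5108. SE = 0.5108 / pooled non-centrality.

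- Smallest (I, 10% quitting): 0.5108 / 5.335 = 0.0957.
- Largest (B, 30% quitting): 0.5108 / 4.811 = 0.1062.

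**4. Effect of an assumed logging shift**

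No document gives a logging shift; the sizes below are assumptions. If logging after the intervention changes by a factor k, the observed ratio is the true ratio × k. With no true effect, the chance of significance is Φ(|ln k|/SE − 1.960) + Φ(−|ln k|/SE − 1.960).

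| Assumed shift, true ratio 1 | abs(ln k) | SE 0.0957 | SE 0.1062 |
|---|---|---|---|
| 10% fewer logged | 0.1054 | 0.196 | 0.168 |
| 20% fewer logged | 0.2231 | 0.645 | 0.556 |
| 20% more logged | 0.1823 | 0.48 | 0.40 |

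The nominal value is 0.05. The last row would be significant in the direction of harm.

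With a true ratio of 0.60 and 20% more logging, the observed ratio is 0.60 × 1.20 = 0.72. Power is then Φ(0.3285/0.0957 − 1.960) = 0.93 or Φ(0.3285/0.1062 − 1.960) = 0.87. With 20% less logging, the same true ratio would read as 0.60 × 0.80 = 0.48.

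The SE for I treats its effect as a constant 0.6, whereas item 14 assumes a relapse to 0.7 in arms 1, 4 and 7. If the fitted effect averages over that relapse, the SE for I would be smaller than shown.

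**The case against.** Unblinded self-report is hard to avoid when a training trial counts workplace aggression, and the protocol is open about it: 17a says participants are not blinded, and 18a labels the log as self-reported. The article never claims protection from detection bias in those words. The plan also has partial mitigations: incidents by type are a secondary endpoint, and item 20a plans mixed logistic models for severe events. All of this stands. It makes the defect an unscoped sentence, not concealment, but the sentence remains untrue for the primary outcome.

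Three stronger readings are tempting and not supported.

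- **That no blinding exists anywhere in the trial.** Research assistants collect data, and they could be kept unaware of status for the interviewer-administered scales, even if the displayed code of conduct makes that fragile.
- **That the analyst is unblinded because the statistician holds the allocation.** No section says the two are the same person, and a shared institution does not show it. An unblinded analyst would in any case introduce bias in analysis, not in detection of incidents.
- **That a false benefit is the likely result.** The one mechanism that can be read from the text, learning to identify tension, points to more logging after training, which would attenuate a true benefit. Under-logging is possible, but the documents neither describe nor quantify it.

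**Conclusion.** The concern holds for the primary incident count and the severity score: 17a attributes to them a blinding that 17a and 18a together rule out. Analyst blinding is undetermined. For other outcomes, assessor blinding may be achievable.

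The size of any resulting bias is unknown, and so is its direction. The figures show only that the design is sensitive: shifts of 10–20% in logging, small beside the planned 40% reduction, could produce a significant result where there is no effect, or weaken a real one. They rest on assumed shifts, two-sided 5% testing and a standard error inferred from Table 2, and they are not estimates of what will happen. The misstatement itself depends on none of them. It should be corrected, and the correction is cheap.

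**What to change.** 1. In item 17a, limit the assessor-blinding statement to outcomes that have a separate assessor, and name them.
2. State there that the incident count and its severity rating are participant-reported and unblinded, and that a change in reporting threshold is a limitation in either direction.
3. State whether the data analyst is a different person from the statistician who generates and holds the sequence.
4. Prespecify the primary mixed Poisson model fitted to physical incidents alone as a supportive analysis, reported beside the primary result. Describe it as less dependent on a reporting threshold, but still self-reported by the same unblinded workers and less precise. It should not act as a condition for concluding that violence fell.

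The first three are changes of wording. The fourth needs one more model on data that the log already records, since each entry distinguishes verbal from physical assault. Its precision cannot be worked out in advance, because the protocol does not give the expected share of physical incidents.

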### Procedure for unblinding if needed {17b}

N/A. Procedures for unblinding do not apply to the trial design.

## Data collection and management

### Plans for assessment and collection of outcomes {18a}

In all arms, incidence and severity of episodes of violence will be collected by each consenting HCW (self-reported) via the *Aggression log*, longitudinally, during the initial observation period (P1) of 12 weeks and during the whole duration of the trial. This instrument will capture the frequency and description of the incident experienced during the working hours and will allow the staff to judge the severity of the incident via a 100-mm visual analogue scale (VAS). The *Aggression log*, adapted from Morken et al., was customized based on qualitative insights, and simplified for user-friendliness, incorporating feedback from healthcare personnel and experts in both countries, ensuring efficient reporting despite demanding work pressure [50]. The tool will be completed by the HCWs and each time the HCWs are exposed to aggressive behaviors, defined as any verbal, non-verbal, or physical behavior that was threatening or physical behavior that was adding arm. Entries will include time of incident, perpetrator’s gender, type of assault, whether verbal (e.g. verbal threat, insult) or physical, means used by the aggressor and consequences for the victim. Participants will be assured confidentiality and anonymity of their responses through unique identifiers, and a secure reporting system will be established.

Successively, secondary outcomes will be measured on the same individuals, from each cluster at discrete point in time using standardized and validated questionnaires and scales. The total length of the study trial will vary across arms. HCWs from arms with the longest trial duration will have four discrete outcome measurements taken, i.e., at baseline, during the last 2 weeks of P1, at 22 weeks after the intervention introduction, at the end of observation period 2 (P2) (first follow-up FU1), at 47 weeks at the end of P3 (FU2), and at 72 weeks from the intervention, at the end of P4 (FU3) (Fig. 1). These arms will have an overall trial duration of 87 weeks. Arms with shorter durations will have fewer outcome measurements taken. Data collection tools will be programmed electronically on tablets, using Open Data Kit (ODK) [51]. The questionnaire will be administered in French in DRC and in Arabic or English in Iraq and will include questions about HCWs exposure to violence, either to physical or verbal violence, the immediate actions taken if any after being exposed to violence, whether they reported the violence, or if any action was taken by the authorities. Questions will also inquire about family members’ or colleagues’ exposure to any sort of violence and the perspective of the participants about the future of this phenomenon. The questionnaire will also include validated scales to assess different psychosocial variables as for example, post-traumatic stress disorders (PTSD), the level of burnout, or measures of quality of life and cost data (see Table 3 Participant timeline).

**Table 3 Tab3:** Sample size

	Iraq			DRC		
Drop out probability within an observation period	10%	20%	30%	10%	20%	30%
Expected number of health care workers to be recruited	340	415	491	212	259	307

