## Statistical methods

### Statistical methods for primary and secondary outcomes {20a}

Descriptive statistics will be used to summarize the characteristics of HCWs. For the analysis of observed event data, the model applied with the simulated data sets will again be used. HCWs will be considered as separate observational units. For each observation period, the time during which a HCW was under observation will be used as individual offset variable and each HCW will get his/her own random intercept in the analysis. Additional analyses will involve scores reported by the HCW at the end of each period or even during periods. Mixed linear models with robust standard error estimates involving analogous terms as the mixed Poisson regression models will be used; however, without accounting for the time, a HCW has been active during a given period. Analyses addressing the occurrence of severe events will be conducted using mixed logistic regression models. In this case, the outcome is 1 if the respective health worker experienced a severe event in the respective period and 0 otherwise. The structure of these models will be analogous to the one of the models for event rates and scores.

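### A VAS-based severity result cannot by itself separate less severe violence after training from a changed rating of the same incidents

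*Protocol article*

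**What the plan says.** Severity is part of the overarching goal in Objectives {7}, and the comparator section {6b} sets severity before the intervention against severity after it within each cluster. In Plans for assessment and collection of outcomes {18a}, the Aggression log is completed by the HCW who had the incident and "will allow the staff to judge the severity of the incident via a 100-mm visual analogue scale (VAS"). No other severity measure is named. The same log also records "type of assault, whether verbal (e.g. verbal threat, insult) or physical, means used by the aggressor and consequences for the victim".

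For severe events, Statistical methods {20a} plans a mixed logistic model in which "the outcome is 1 if the respective health worker experienced a severe event in the respective period and 0 otherwise". It does not say how a severe event is defined.

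On the raters, {17a} states: "It will not possible to blind the trial participants to the intervention". On the training, {11a} describes it as "designed to provide HCWs with the ability to identify tense situations from the outset and to develop skills to defuse them", and one of its five modules covers the causes and effects of violence in health care. The Discussion expects trained staff to be more confident, less burnt out and more empathic.

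**The concern.** The person who rates severity is the person who is trained. After training, the same incident may be rated lower because the HCW feels more able to cope, or higher because the HCW notices more. Either shift would begin when the training begins, so it would coincide with the exposure whose effect is estimated. The severity result would then mix two things: a change in the violence and a change in the yardstick. A downward shift would look like benefit, and an upward shift could hide one.

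The log already holds descriptive fields that depend much less on appraisal, but nothing in the article links them to severity.

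**Working it through.** **1. The plan's own figure.** The article gives no figure for severity: no expected VAS mean or SD, no cut-off and no power. There is nothing to reproduce. The only inputs that can be borrowed come from Sample size {14}: one event per HCW and 6-month period without intervention, and an SD of 0.2 on the log scale for facilities and for HCWs.

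**2. Where a rating shift would enter.** Suppose the recorded VAS equals the rating the HCW would have given untrained, plus δ once trained.
- The random intercept for each HCW ({20a}) absorbs a rater who is always strict or always lenient. It is constant over time, so it cannot absorb δ.
- Using each site as its own control ({6b}) removes stable site differences, not a change that starts at crossover.
- A period effect, if the model has one, is shared by trained and untrained clusters in the same period, so it does not absorb δ either.
- Blinding in {17a} ("The data analyst and the outcome assessors will be blinded to the status of the intervention at the time the outcome is determined") cannot reach a VAS mark made by an unblinded HCW.

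So δ, if it is not zero, is attributed to the training.

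**3. Illustration of size.** Assumed, because the documents give none of these: VAS normal with mean 50 mm and SD 25 mm, severe at 70 mm or more, shift δ of 5 or 10 mm either way. From {14}: λ = 1 incident per period. True incidents are identical before and after.

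- Share of incidents rated severe: s = 1 − Φ((70 − 50 − δ)/25)
- Probability of any severe event in the period: P = 1 − exp(−λs)
- Odds: P/(1 − P) = exp(λs) − 1

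| δ (mm) | s | P | odds | odds ratio vs δ = 0 |
|---|---|---|---|---|
| 0 | 0.212 | 0.191 | 0.236 | 1 |
| −5 | 0.159 | 0.147 | 0.172 | 0.73 |
| −10 | 0.115 | 0.109 | 0.122 | 0.52 |
| +5 | 0.274 | 0.240 | 0.316 | 1.34 |
| +10 | 0.345 | 0.291 | 0.411 | 1.74 |

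Letting λ vary log-normally with variance 0.2² + 0.2² = 0.08, as in {14}, gives 0.73, 0.52, 1.33 and 1.74, which is practically the same.

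**4. Range.** With mean 50, SD 20 to 30 and cut-offs 60 to 80 mm, a 5 mm downward shift gives 0.59 to 0.81 and a 10 mm downward shift 0.33 to 0.64. A second grid (mean 40 or 50, SD 20 or 25, cut-off 50 or 70 mm, variable λ) gives the same downward ranges. Its upward ranges are 1.21 to 1.61 for 5 mm and 1.42 to 2.48 for 10 mm.

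**5. Scale.** The planned incidence effect is a rate ratio of 0.6, which is not an odds ratio. On the same footing, a true fall to λ = 0.6 with s unchanged at 0.212 gives λs = 0.127, odds exp(0.127) − 1 = 0.136, and an odds ratio of 0.136/0.236, about 0.57. Under these assumptions a 10 mm rating shift (0.52) would be of the same order as that planned effect.

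**The case against.** The strongest reply is that {20a} never ties a severe event to the VAS. A definition built on type, means and consequences would fit the text equally well, and a condensed article may leave that definition to the full protocol or analysis plan. This stands: the missing definition is no error, and the VAS reading is an inference from its being the only severity measure named. But any VAS-based severity result, with whatever cut-off, has the problem described.

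Other replies also stand in part.
- The primary objective and endpoint concern incident counts. VAS severity and severe events are in neither endpoint list in Outcomes {12}, so calling severity half of what the trial tests would go beyond the documents. It is part of the stated goal, not of the endpoint hierarchy.
- Incident counts by type are already a secondary endpoint and need no VAS.
- The mechanism rests on the training's content. It bears on the training (I) and the refresher (R). The board (B), estimated as a separate effect, is not exposed in the same way.
- The documents nowhere show that training changes ratings. That is an inference from the aims in {11a} and the expectations in the Discussion.
- The alternative fields are self-reported too, and an incident enters the log only if the HCW regards the behaviour as threatening or harmful. No rule on those fields removes that threshold.

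A reader might infer that the planned severe-event result is biased, or that the VAS should be dropped. The documents support neither: no shift is documented, and perceived severity is a legitimate outcome in its own right.

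**Conclusion.** The point holds as one of interpretation. If severity is judged by the VAS, a change after training (I or R) cannot by itself be attributed to the violence rather than to the rating, and neither the random intercepts, the within-site comparison nor the stated blinding resolves this. The direction is unknown. The odds ratios (0.33 to 0.81 for downward shifts of 5 to 10 mm, 1.21 to 2.48 for upward shifts) show only what such shifts would do under assumed VAS means, SDs and cut-offs; they do not estimate the bias in this trial. The primary endpoint is outside this point. A modest addition to the analysis is warranted because severity belongs to the stated goal and less appraisal-dependent information is already collected.

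**What to change.** In {18a} and {20a}, before outcome analysis:

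1. Add a severe-event outcome defined by a fixed rule on fields already in the Aggression log: type of assault, means used and consequences for the victim. Include explicit verbal threats by name, so that serious non-physical incidents are not lost.
2. Apply the rule by program, identically in all periods, and analyse it in the planned mixed logistic model.
3. Report the VAS beside it, labelled *perceived severity*, and read both with the type-specific incident counts in Outcomes {12}.
4. Claim reduced severity of violence only if the rule-based outcome supports it.

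The cost is wording and one further model; no new data are needed, so the change remains possible after data collection if the rule is fixed before outcomes are analysed. The article names the fields but not their coding, so the rule must be written against the actual form. Bias is reduced, not removed, because these fields are also self-reported and subject to the same threshold for making an entry. The verbal-threat part of the rule needs most care.
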